#### Gender differences: effect of different voices

Gender acts as an independent risk factor for several diseases and disorders. For example, female gender has already been established as a specific risk factor for the occurrence of postoperative nausea and vomiting [14]. The opposite seems to be true for the occurrence of delirium after surgical interventions: In this context, men seem to be more likely to develop POD [15]. With the upcoming awareness for gender sensitive medicine, research has also increasingly focused on the impact of sex differences on the efficacy of therapeutic interventions. For instance, there appear to be discrepancies in the efficacy of hypnosis therapy for smoking cessation when administered to different sexes (Green et al., 2008). However, robust data on gender differences in the effects of suggestive procedures is missing. In particular, no research has been done on gender differences in the effects of hypnotic suggestion when delivered by different voices.

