### Objectives {7}

In the current study, we aim to address the following hypotheses:

Primary hypothesis:Delirium incidence is lower in the intervention group than in the control group

Secondary hypotheses:2)Pain intensity is lower in the intervention group than in the control group3)Intraoperative: NOL values are lower in the intervention group than in the control group4)Postoperative: NRS values are lower in the intervention group than in the control.5)Pain medication consumption p.p. is lower in the intervention group than in the control group6)Postoperative nausea and vomiting (PONV) incidence is lower in the intervention group than in the control group

Exploratory analyzation:7)The above-mentioned effects differ depending on whether the subjects hear a speaker’s voice according to their own gender or not

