### Outcomes {12}

Primary outcome will refer to delirium incidence. Cognitive testing in form of the 4AT [19, 20] as well as the 3DCAM [21] will be performed pre- and postoperatively on all study participants to determine whether the incidence of delirium is lower in the intervention group than in the control group.

The 4AT is a brief (< 2 min) screening tool for delirium and cognitive impairment. It includes four domains: alertness, abbreviated mental test–4, attention (months backwards), and acute change or fluctuating course. A score ≥ 4 suggests possible delirium. The 3D-CAM is a structured, validated instrument based on the Confusion Assessment Method (CAM) algorithm, optimized for administration in approximately 3 min. It evaluates acute onset or fluctuating course, inattention, disorganized thinking, and altered level of consciousness. A diagnosis of delirium according to 3D-CAM requires the presence of features 1 and 2, plus either feature 3 or 4 [21, 22]. Both assessments will be conducted by trained members of the study group. Correct assessment will be ensured by random checks as well as supervision through a psychologist.

As secondary outcomes postoperative nausea will be assessed with the Wengritzky PONV score [23], pain will be assessed using the Numerical Rating Scale (NRS) for subjective measurement and using the NOL index for objective measurement. Medication consumption will be documented by analyzing the patient’s files.

Furthermore, the effect of different speaker voices will be investigated as an exploratory analysis.

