#### Implementation {16c}

Trained junior researchers will enroll participants, while the allocation sequence will be automatically generated by RedCap. In detail, randomization will be conducted in REDCap using permuted block randomization with stratification by gender, resulting in separate randomization lists for male and female participants. This ensured a balanced allocation between intervention and control groups within each gender. The gender stratification was implemented to allow for the preplanned secondary analysis of potential effects related to gender–voice congruence. The PI of the study will perform randomization in the above mentioned way.

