### Data collection and management

#### Plans for assessment and collection of outcomes {18a}

##### Baseline

Patients will be pseudonymized after inclusion. Required data items encompass Montral Cognitive Assessment (MOCA) [25], Frailty-test [26], PONV risk score [23], and continuous medication including pain medication. Additionally, patients will complete the Quality-of-Life questionnaire (SF-36) [27], Geriatric Depression Scale (GDS) [28], and instrumental Activities of Daily Living (iADL) [29].

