### Statistical methods

#### Statistical methods for primary and secondary outcomes {20a}

To ensure normal distribution, the Kolmogorov–Smirnov test will be conducted prior to further analyses. Statistical significance will be considered at a *p*-value < 0.05. The primary outcome (postoperative delirium incidence) and other binary outcomes (e.g., incidence of postoperative nausea and vomiting, PONV) will first be compared between the intervention and control groups using the chi^2^ test. Continuous non-parametric variables will be analyzed with Mann–Whitney *U* tests, and parametric variables with Student’s *t*-test. To account for potential confounding effects of intraoperative and postoperative medication use, detailed data on the type and dosage of analgesics and sedatives will be collected. These variables will be included as covariates in multivariable logistic regression models for binary outcomes (e.g., delirium, PONV) and multivariable linear regression models for continuous outcomes (e.g., postoperative pain scores, NRS; intraoperative NOL index values). Confounders will be selected a priori based on clinical relevance and evidence from previous literature to avoid data-driven overfitting.

Medication-related parameters (e.g., total opioid dose, intraoperative sedative use) will also be analysed descriptively and compared between groups. Sensitivity analyses will be performed to assess the robustness of the results with and without adjustment for these covariates.

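### PONV incidence (hypothesis 6) gets an unadjusted chi-square and a model whose only named covariates arise after randomisation; naming the baseline PONV risk score and gender would add a little precision at no cost

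*Protocol article*

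**What the plan says.** Objectives {7} lists as hypothesis 6: "Postoperative nausea and vomiting (PONV) incidence is lower in the intervention group than in the control group". Statistical methods {20a} says the primary outcome and "other binary outcomes (e.g., incidence of postoperative nausea and vomiting, PONV) will first be compared between the intervention and control groups", with a chi-square test. The same paragraph then turns to the type and dose of analgesics and sedatives given during and after surgery: "These variables will be included as covariates in multivariable logistic regression models for binary outcomes (e.g., delirium, PONV" and others). It adds: "Confounders will be selected a priori based on clinical relevance and evidence from previous literature to avoid data-driven overfitting". It closes with sensitivity analyses with and without the medication covariates.

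Elsewhere the article describes two baseline variables that bear on PONV:

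- **Risk score.** Table 1 (Participant timeline {13}) lists a PONV risk score at the baseline visit, and the Baseline subsection of {18a} lists it too.
- **Gender.** The introduction states that "female gender has already been established as a specific risk factor for the occurrence of postoperative nausea and vomiting [14"], and Implementation {16c} specifies "permuted block randomization with stratification by gender".

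Neither is named as a covariate in {20a}. Sample size {14} gives no PONV rate, effect size or power.

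**The concern.** For a binary endpoint in a randomised trial, the useful covariates are those measured before randomisation that predict the outcome. Here one was collected for exactly this endpoint, and another defines the randomisation strata. The first test uses neither.

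The planned regression does not fill the gap as worded. Drug use during and after surgery arises after allocation, and pain medication consumption is itself an outcome (hypothesis 5). Adjusting for it can absorb part of any effect of the suggestions, and it is no substitute for baseline risk. As written, hypothesis 6 therefore has one analysis that ignores baseline risk and one whose named covariates the intervention may change. The text does not say which of the two decides.

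What is at stake is some power and precision on one secondary hypothesis for which the sample size was not planned.

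**Working it through.** **1. The sample size available.** Sample size {14} takes 248 evaluable patients from pain intensity, d = 0.325, power 0.8, 5% level. A one-sided two-sample comparison needs 2(1.645 + 0.842)²/0.325² ≈ 117, or 118 per group with the calculation routine used. Multiplying by π/3 for a Mann-Whitney test gives 118 × 1.047 = 123.6, so 124 per group and 248 in total. The figure reproduces (one-sided; two-sided would need about 312). It is used below only as the N for PONV.

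**2. Assumptions for PONV.** The article gives none, so these are mine: control rate 20, 30 or 40%; 40% relative reduction; two-sided 5% test (the article does not state the side); 124 per arm.

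**3. Closed form.** With p₁, p₂ the two rates and p̄ their mean,

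power = Φ{ [ |p₁ − p₂| − 1.96 √(2p̄(1 − p̄)/n) ] / √[(p₁(1 − p₁) + p₂(1 − p₂))/n] }.

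If baseline covariates explain a share R² of the variance of PONV, replace n by n/(1 − R²). Worked case, 30% against 18%:

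- Unadjusted, n = 124: (0.12 − 1.96 × 0.0542)/0.0537 = 0.255, power 60.1%.
- R² = 0.10, n = 137.8: (0.12 − 1.96 × 0.0515)/0.0509 ≈ 0.376, power 64.6%.

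| Control → intervention | Chi-square | R² = 0.05 | R² = 0.10 | R² = 0.15 |
|---|---|---|---|---|
| 20% → 12% | 40.4% | 42.1% | 44.1% | 46.1% |
| 30% → 18% | 60.1% | 62.3% | 64.6% | 67.2% |
| 40% → 24% | 77.4% | 79.5% | 81.6% | 83.7% |

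**4. Simulation.** 3,000 trials per setting, N = 248, half women, 1:1 within gender. The assumed odds ratios for gender and per SD of the rest of the risk score were 2.0 and 1.5 (weak), 2.5 and 2.0 (moderate), 3.0 and 2.5 (strong). Power for the chi-square, the logistic model with gender, and the logistic model with gender and score:

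| Control rate | Strength (R²) | Chi-square | + gender | + gender and score | Gain, last minus first (points) |
|---|---|---|---|---|---|
| 20% | weak (0.043) | 41.8% | 40.7% | 41.5% | −0.3 |
| 20% | moderate (0.097) | 40.4% | 39.9% | 43.5% | +3.1 |
| 20% | strong (0.149) | 43.1% | 42.7% | 46.3% | +3.2 |
| 30% | weak (0.055) | 60.9% | 61.1% | 62.0% | +1.1 |
| 30% | moderate (0.118) | 60.1% | 60.6% | 63.5% | +3.4 |
| 30% | strong (0.175) | 61.2% | 61.9% | 67.0% | +5.8 |
| 40% | weak (0.061) | 78.6% | 79.0% | 80.0% | +1.4 |
| 40% | moderate (0.129) | 78.5% | 79.5% | 82.5% | +4.0 |
| 40% | strong (0.188) | 77.8% | 79.0% | 84.9% | +7.1 |

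Simulation error is about 1 point. Gender alone moves power by −1.1 to +1.2 points.

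**5. Validity.** With no treatment effect, the rejection rate was 4.3 to 5.2% for the chi-square and 4.7 to 5.4% for the model with gender and score. Both hold the 5% level within simulation error.

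**6. Precision.** Interval width was not simulated. To first order the interval for a risk difference narrows by 1 − √(1 − R²): 2.5% at R² = 0.05, 5.1% at 0.10 and 7.8% at 0.15.

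**The case against.** The strongest reply is that adjustment is planned. The chi-square comes only first, a logistic model for PONV is named, and its confounders are to be chosen a priori on clinical relevance and literature. Gender fits that criterion on the article's own evidence, and a PONV risk score plainly would too. An exact covariate list is often left to an analysis plan, which is not shown here. This stands in part: a reader might infer that the trial will leave baseline risk out altogether, and the text does not support that. What remains is that the only covariates actually named are post-randomisation ones. The a priori sentence follows directly on medication use, and the sensitivity analyses concern the same medication variables.

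Second, the gain is small and rests on assumed rates. This stands. All groups receive PONV prophylaxis unless contraindicated, so a low control rate is plausible. At 20% the hypothesis is underpowered with or without adjustment (40.4% against 42.1 to 46.1%).

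Third, a reader might infer that ignoring a stratification factor spoils the chi-square, or that leaving gender out is costly. Neither holds under the settings examined: the error rate is sound and gender alone changes almost nothing. Nor should one expect a narrower odds-ratio interval, because the adjusted odds ratio is a different, conditional quantity. The precision argument applies to a standardised risk difference.

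Fourth, the baseline "PONV risk score [23"] and the postoperative "Wengritzky PONV score [23"] share a citation. One might conclude that the baseline instrument is unidentified. Table 1 lists the two separately, and the cited source may cover both, so this is at most clerical.

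**Conclusion.** The point holds as a modest efficiency matter on a secondary endpoint. The chi-square is a valid test, and the article claims no PONV power that could fail. Under a 40% relative reduction, control rates of 20 to 40%, N = 248 and a two-sided 5% test, adding gender and the baseline risk score is worth about 0 to 7 power points. Where in that range it falls depends on how strongly the score predicts PONV, which the article does not tell us. The medication-adjusted model, with the covariates it names, does not supply this gain and should not be the deciding analysis. Severity: optional, low-cost improvement.

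**What to change.** Before unblinding, state in {20a} or the analysis plan that:

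- the main analysis of hypothesis 6 is a logistic regression of PONV on arm, gender (the randomisation stratum) and the baseline PONV risk score, reported as a standardised risk difference with a 95% CI;
- the chi-square is the supportive, unadjusted result;
- models adjusted for intraoperative or postoperative medication are exploratory.

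While the text is open, name the preoperative risk score and check its reference. The cost is a few sentences and a short standardisation step in the analysis; no new data are needed. Little is lost if the score proves weak: the weakest setting simulated at a 20% control rate showed −0.3 points, within simulation error.

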## Methods: participants, interventions and outcomes

### Study setting {9}

All data will be collected in Germany. Leading center of the trial is the hospital of the Munich Ludwig-Maximilians-University (LMU). Further data is planned to be collected in the hospital of the Ruhr University Bochum as well as in the Heidelberg university hospital.

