### Sample size {14}

Based on the primary endpoint analysis, the sample size was calculated as follows:

At the university hospital, LMU Munich, a delirium incidence of approx. 25% can be assumed for electively orthopedic surgery. By means of therapeutic suggestion may be reduced by at least 50%. The calculation in G*Power [24] using the z-test “Difference between two independent proportions” results in a sample size of 110 subjects per group for a design in which the intervention group and control group are of equal size, with a required power of at least 0.8 and a significance level of 5%. This results in a total of 220 subjects.

Based on the results of the study by Nowak et al. 2020 [11], we also calculated the sample size needed to detect effects of the intervention on pain expression, which are of great interest in the secondary endpoint analysis: For effects on opioid use, an effect size of *d* = 0.36 is assumed. For a required power of 0.8 at a level of significance at 5%, a group size of at least 101 subjects is needed. For effects on pain intensity, an effect size of 0.325 can be calculated using G*Power based on the mean values and standard deviations given in the original work. When power is set at 0.8 and significance level at 5%, the resulting sample size amounts to a total of 248 subjects.

In addition to the effect of the intervention on delirium incidence, the effect on pain severity is also of great interest as a (secondary) endpoint. Hence, the larger calculated sample number (*n* = 248) is chosen as a further basis for calculation to be able to achieve sufficiently good power for the secondary endpoints as well.

To ensure that the calculated minimum power will be achieved, there is a need to take possible drop-outs into account. Therefore at least 10% more subjects will be necessary, which results in a total of 273 participants. In consideration of the balanced design, the final target equals in a rounded up total number of 280 patients.

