### Assignment of interventions: allocation

#### Sequence generation {16a}

Included patients will be divided as follows: 1:1 (intervention vs. control group) and within the intervention group 1:1 to a speaker with the same gender (sGS) vs. a speaker with a different gender (dGS). Thus, the only factor influencing assignment is patient gender.

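### The primary delirium comparison is an unadjusted chi-square test, and the only adjusted model described uses post-randomisation medication; a model with gender and a few baseline covariates would recover a modest amount of power

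*Protocol article*

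**What the plan says.** **Test.** Under Statistical methods {20a}, delirium and the other binary outcomes "will first be compared between the intervention and control groups using the chi^2^ test". The threshold is given as "Statistical significance will be considered at a *p*-value < 0.05", with no statement of sidedness.

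**Adjusted models.** The same section then plans multivariable logistic regression for binary outcomes, delirium included. The covariates it names are type and dose of analgesics and sedatives used during and after surgery. It adds that confounders will be chosen in advance on clinical grounds and from the literature, without naming any. Sensitivity analyses with and without the medication covariates are promised.

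**Allocation.** Implementation {16c} states that "randomization will be conducted in REDCap using permuted block randomization with stratification by gender", and Sequence generation {16a} concludes: "Thus, the only factor influencing assignment is patient gender". Centre is therefore not a stratification factor, although Study setting {9} says: "Further data is planned to be collected in the hospital of the Ruhr University Bochum as well as in the Heidelberg university hospital".

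**Baseline data.** Table 1 and the Baseline paragraph of {18a} list MoCA, a frailty screen and the Charlson index (the last in Table 1 only). Age is known from eligibility.

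**Planning assumptions.** Sample size {14} states "a delirium incidence of approx. 25% can be assumed for electively orthopedic surgery", assumes that this is halved, and sizes the trial "with a required power of at least 0.8 and a significance level of 5" per cent.

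**The concern.** When randomisation is stratified on a factor that predicts outcome, an analysis that ignores the factor overstates the standard error. The Background says that men appear more prone to postoperative delirium, so the protocol itself treats gender as prognostic. The same logic applies to baseline cognition, frailty, comorbidity and age: conditioning on them would sharpen the treatment comparison at no cost in patients.

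The regression in {20a} does not fill this gap, because its named covariates are measured after allocation. Hypothesis 5 in Objectives {7} predicts that the intervention lowers pain medication use. Adjusting for that use can remove or distort part of the effect being estimated.

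What is at stake is efficiency in a trial whose two-sided power for its primary endpoint is below the stated 80%, and the lack of any adjusted estimate of delirium risk that rests on baseline information only.

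**Working it through.** **Inputs from the protocol.** Control rate p1 = 0.25; intervention rate p2 = 0.125 (half of p1); alpha 0.05; power 0.80; stated size 110 per group; planning total 248 (124 per arm); target 280 (140 per arm).

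**Step 1: the stated figure.** With mean rate 0.1875, the pooled z-test gives

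n = [z_α √(2 × 0.1875 × 0.8125) + 0.8416 √(0.25 × 0.75 + 0.125 × 0.875)]² / 0.125²

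The two roots are 0.5520 and 0.5449. The result is 152 per group two-sided (z = 1.960) and 120 one-sided (z = 1.645). Unpooled and arcsine versions give 150 and 118. None returns 110. The value 110 appears only one-sided with the intervention rate rounded to 12%.

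**Step 2: power of the unadjusted test.** Power = Φ[(0.125 √n − z_α × 0.5520) / 0.5449].

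| Per arm | Two-sided | One-sided |
|---|---|---|
| 110 | 66.3% | 77.0% |
| 124 | 71.5% | 81.3% |
| 140 (no dropout) | 76.7% | 85.3% |

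A 2×2 chi-square test is two-sided by construction, so the two-sided column applies to the plan as written.

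**Step 3: approximate gain from adjustment.** Treat adjustment as raising n to 124/(1 − R²), where R² is the share of outcome variance explained (assumption).

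| R² | Effective n per arm | Power |
|---|---|---|
| 0 | 124 | 71.5% |
| 5% | 130.5 | 73.7% |
| 10% | 137.8 | 76.0% |
| 20% | 155 | 80.8% |

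For gender alone, assumed odds ratios of 1.5 and 2 correspond to R² of about 0.6% and 1.8%. Power then moves only to 71.8% and 72.3%.

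**Step 4: simulation.** Marginal rates 25% and 12.5%, two-sided 0.05, allocation balanced within gender, 6,000 replicates. Assumed: gender log odds ratio 0.5; three centres in proportions 60/20/20 with log odds of 0, +0.4 and −0.4; four equally weighted baseline predictors. AUC is that of all these factors combined. Adjusted results are logistic likelihood-ratio tests.

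| Per arm | AUC | Chi-square | Gender + centre | + four baseline |
|---|---|---|---|---|
| 124 | 0.66 | 74.2% | 75.0% | 75.7% |
| 124 | 0.72 | 72.5% | 73.2% | 76.9% |
| 124 | 0.78 | 72.4% | 72.9% | 80.1% |
| 140 | 0.66 | 77.8% | 78.9% | 79.8% |
| 140 | 0.72 | 77.2% | 77.9% | 81.1% |
| 140 | 0.78 | 76.9% | 77.9% | 84.9% |

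At 124 per arm the full gains are 75.7 − 74.2 = 1.5, 76.9 − 72.5 = 4.4 and 80.1 − 72.4 = 7.7 points. A leaner model at 124 per arm, with gender and one combined baseline score (4,000 replicates), gained 1.6, 4.5 and 6.7 points at AUC 0.65, 0.71 and 0.78. Adjusting for gender alone in that simulation gained 0.1 to 0.2 points.

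**Step 5: validity.** With no treatment effect, the chi-square test rejected in 4.4% to 4.8% of replicates. The adjusted tests rejected in 4.3% to 5.2%.

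**Step 6: room for covariates.** Expected events at 124 per arm: 124 × 0.25 + 124 × 0.125 = 31 + 15.5 = 46.5. A model with arm, gender, two centre terms, age, MoCA and frailty has 7 parameters, or 46.5/7 = 6.6 events each. Arm, gender, age and one of MoCA or frailty has 4, or 46.5/4 = 11.6.

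**The case against.** An unadjusted chi-square test planned in advance for a 1:1 randomised comparison is a legitimate primary analysis. It controls the error rate, and chance imbalance between centres is already covered by that error rate. The protocol also plans a multivariable model with confounders chosen in advance, and naming baseline covariates could be left to an analysis plan that is not shown. All of this stands, and it makes the point one of efficiency.

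It does not dispose of the point. The article itself fixes the test, and the covariates it does name are post-randomisation. A general promise to choose confounders in advance does not turn that model into a sound adjusted primary analysis.

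A reader might infer three stronger claims that the documents do not support:

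- **Ignoring gender and centre costs material power or biases the result.** The simulated cost is 0 to 1 point. The protocol gives no delirium rates by centre, and the fact that analgesia and PONV prophylaxis follow institutional practice does not show that delirium differs by centre.
- **The baseline measures are strong predictors and would restore 80% power.** The protocol gives no figure for predictor strength, and excluding dementia, MoCA below 17 and preoperative delirium narrows the cognitive range. At 124 per arm, 80% is reached only at an AUC of about 0.78.
- **The choice of test causes the power shortfall.** Most of it comes from Sample size {14}: 220 patients against 2 × 152 = 304 for a two-sided test, a gap of 84.

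**Conclusion.** The point holds as a recommended improvement. The primary comparison takes no account of the stratification factor or of baseline information already collected, and the adjusted model that is described conditions on variables the intervention may change. The unadjusted test is valid and slightly conservative.

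At 124 per arm, the gain is about 0 to 1 point of power from gender and centre, and about 1.5 to 8 points once baseline predictors are added. That range rests on an assumed AUC of 0.66 to 0.78, on 25% against 12.5%, and on two-sided testing. If the baseline measures predict weakly, the gain is near the bottom of the range. Adjustment mitigates the shortfall left by the sample size section but does not replace correcting it.

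**What to change.** In {20a}, make the primary analysis a pre-specified logistic regression of delirium on arm, gender and a small named set of baseline covariates, for example age and either MoCA or frailty. Add centre only if the event count allows. Report a standardised risk difference with 95% CI. State that medication used during or after surgery is kept out of this model, and retain the chi-square test as a supportive analysis.

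The cost is a change of wording, with no extra patients or measurements. The small downside is that about 47 events support few covariates, so the list must be fixed before unblinding. Correct the sample size calculation in {14} as a separate matter.

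### Models that adjust for intraoperative and postoperative drug doses do not estimate the effect of the suggestions, and agreement with and without that adjustment is not a test of robustness

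*Protocol article*

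**What the plan says.** All references are to the protocol article. Section {20a} starts with unadjusted comparisons. Delirium and other binary outcomes "will first be compared between the intervention and control groups using the chi"-squared test, and continuous outcomes by Mann–Whitney or t-test.

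It then adds regression models. The reason given is "To account for potential confounding effects of intraoperative and postoperative medication use", for which type and dosage of analgesics and sedatives are recorded. On their use: "These variables will be included as covariates in multivariable logistic regression models for binary outcomes (e.g., delirium, PONV"). NRS and NOL are handled in the same way, by linear instead of logistic regression. The section closes with: "Sensitivity analyses will be performed to assess the robustness of the results with and without adjustment for these covariates".

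Four other places bear on this:

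- Objectives {7} makes lower drug use a secondary hypothesis: "Pain medication consumption p.p. is lower in the intervention group than in the control group".
- Sample size {14} puts a size on it: "For effects on opioid use, an effect size of *d* = 0.36 is assumed".
- The plans for outcome collection {18a} tie nurse-controlled analgesia on the ward to an NRS of 3 or higher.
- The participant timeline {13} places allocation at the baseline visit, and the intervention description {11a} starts the audio after intubation.

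**The concern.** A confounder of a treatment comparison is a cause of the outcome that also differs between arms for reasons other than treatment. Randomisation removes such differences in expectation, and a dose given after allocation cannot bring them back. If doses differ systematically between arms, the intervention caused the difference, directly or through its effect on pain or delirium.

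Analgesic dose therefore lies on the path from intervention to outcome. Holding it fixed takes out whatever part of the effect runs through it. Ward analgesia also responds to the pain score, so an NRS model adjusted for that dose conditions partly on a consequence of its own outcome. If dose and outcome share unmeasured causes, the adjusted coefficient is not a clean direct effect either.

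Two things are at stake. The adjusted odds ratios and mean differences could be read as the better estimates of the effect. And the comparison with and without adjustment is offered as evidence of robustness. If the intervention works partly by lowering opioid need, the two results should differ. If they agree, that does not validate the adjusted model.

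**Working it through.** **The plan's own figures.** Section {14} needs 101 per group for d = 0.36 on opioid use and 248 in total for d = 0.325 on pain. Both reproduce as a one-sided 5% Mann–Whitney calculation with 80% power, that is, the t-test size divided by the asymptotic relative efficiency of 0.955:

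- d = 0.36: 96.09 / 0.955 = 100.6, so 101 per group.
- d = 0.325: 117.75 / 0.955 = 123.3, so 124 per group and 248 in total.

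The plan thus assumes that treatment shifts the covariate by about a third of a standard deviation, and it sizes a comparison on that shift.

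**Order of events.** Allocation is at baseline, induction and intubation follow, then the audio, further intraoperative dosing and postoperative dosing. All the doses in question come after allocation. Those given up to intubation also come before the audio starts.

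**Inputs for the pain illustration.** Effect on pain δY = 0.325 and on opioid dose δM = 0.36, both reductions in within-arm SD units ({14}). Size: 124 per arm (248 / 2). The within-arm correlation ρ between dose and pain is not in the protocol; I assume 0.3, 0.5 and 0.7.

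**Formulas.** In a linear model with dose as covariate and unit within-arm SDs:

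- adjusted effect = δY − ρ·δM
- residual SD = √(1 − ρ²)
- power from a t-test on adjusted effect / residual SD, 124 per arm, two-sided 5%

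| ρ (assumed) | Adjusted effect | Share removed | Residual SD | Power |
|---|---|---|---|---|
| unadjusted | 0.325 | – | 1 | 72% |
| 0.3 | 0.325 − 0.108 = 0.217 | 33% | 0.954 | 43% |
| 0.5 | 0.325 − 0.180 = 0.145 | 55% | 0.866 | 26% |
| 0.7 | 0.325 − 0.252 = 0.073 | 78% | 0.714 | 13% |

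Allowing for the correlation between treatment and dose lowers the last three powers to 42%, 25% and 12%. With a one-sided 5% test, which the plan's figures imply but the text does not state, the column reads 82%, 56%, 37% and 20%.

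**Direction.** The table assumes that patients in more pain receive more drug, as the NRS trigger suggests. If pain relief from the drug dominated and ρ were −0.3, the adjusted effect would be 0.325 + 0.108 = 0.433, an overstatement. The sign of the bias is therefore not fixed.

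**Delirium.** The protocol gives no relation between dose and delirium, so I attach no size to the bias there. Expected events at 124 per arm, with the plan's 25% and half of that, are 124 × (0.25 + 0.125) = 46.5, about 46. This limits how many covariates a delirium model can carry.

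**The case against.** The strongest reply is that the primary comparison is untouched. The chi-squared test comes first, uses no covariates, estimates the total effect and matches the two-proportion basis of the delirium sample size. The same holds for the unadjusted tests of the continuous outcomes, and results with and without adjustment stay visible. All of that stands. A reader might infer that the primary analysis is biased or loses the power shown above. The document does not support this: the loss belongs to the dose-adjusted pain model alone.

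Other tempting readings also go too far:

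- *The intervention is hypothesised to change sedative doses.* The hypothesis covers pain medication only. Sedatives are a problem because they too are given after randomisation.
- *NOL will certainly be adjusted for postoperative doses, which come after it.* The wording makes no exception, but {20a} gives no covariate list per outcome.
- *A true effect would be declared not robust.* The plan sets no rule for reading a change after adjustment.

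Two defences do not rescue the models. Choosing covariates in advance prevents data-driven selection, but it does not turn a mediator into a confounder. The background section does describe pain as measured by analgesic consumption at a defined pain level, so there is reason to look at the two together. Entering one as a covariate for the other is not a valid way to do so.

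**Conclusion.** The point holds for the dose-adjusted models and for the with-and-without comparison. Those models do not estimate the total effect of the suggestions on delirium, PONV, NRS or NOL. The protocol does not say which result decides if adjusted and unadjusted results differ, and agreement between them shows nothing about robustness.

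For pain, 33% to 78% of the planned effect is removed under the assumed correlations of 0.3 to 0.7. Those figures rest on the plan's two effect sizes, a linear model and a positive dose–pain relation. The structural error depends on none of these: it follows from the timing of the doses and from the protocol's own hypothesis on pain medication.

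**What to change.** In {20a}:

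1. State that the comparison without medication covariates is decisive for every outcome.
2. Remove intraoperative and postoperative analgesic and sedative doses from the models that estimate the intervention effect, and stop calling them confounders.
3. Analyse medication consumption as an outcome, as the hypothesis in {7} already requires.
4. If dose-adjusted models are kept, label them exploratory mediation analyses, state their assumption of no unmeasured common causes of dose and outcome, and do not use them as a robustness criterion.
5. If covariate adjustment is wanted, use a short prespecified set of pre-randomisation variables already collected, for example the stratification factor gender plus age or the baseline value of the outcome. Keep it small for delirium, with about 46 events expected. A long list would replace one problem with another.

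The cost is a change of wording before the analysis. No new data are needed, and the sample size does not change.
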